### Participant timeline {13}

Table 3 summarises the participant timeline including the assessments at each visit.

**Table 3 Tab3:** Visit schedule and assessments

	**Screening** **(Baseline day)** **−28–0**	**Visit 1** **Rando** **Day 0**	**Visit 2 ****Intervention** **Day ****1–7** after Rando (only TIPS group)	**Visit 3 ****Discharge ****4 days** after intervention** (+ 7/−2 days) **(only TIPS group))	**Visit 4 ****M1 ****1 month **after Rando **(+ 2 weeks)**	**Visit 5 ****M3 ****3 months **after Rando **(± 4 weeks)**	**Visit 6 ****M6 ****6 months **after Rando **(± 4 weeks)**	**Visit 7 ****M9 ****9 months **after Rando **(± 4 weeks)**	**Visit 8 ****M12** **12 months** after Rando **(± 4 weeks)**	**FU ****Every 6 Month until EOS***^**2**^
Informed Consent	x									
Registration (i.e. entry of first data in eCRF)	x									
Inclusion-/Exclusion criteria	x									
Randomisation		x								
Demographics	x									
Medical history	x									
Physical examination, vital signs	x									
Pregnancy test	x									
12-lead ECG	x									
Colour Doppler ultrasound	x			x	x	x	x	x	x	
Echocardiography (TTE)	x						x			
TIPS (according randomisation)			x							
Laboratory (haematology, clinical chemistry, coagulation)	x**		**:	x	x	x	x	x	x	
Urinalysis	x						x			
Clinical scores^1^	x			x^1^	x^1^	x^1^	x^1^	x^1^	x^1^	
Paracentesis	(x)									
SF-36, CLDQ	x						x		x	
Survival status, liver transplantation				x	x	x	x	x	x	x
Concomitant medication	x	x	x	x	x	x	x	x	x	
(S)AEs	x	x	x	x	x	x	x	x	x	x

*CLDQ *Chronic Liver Disease Questionnaire, *ECG* electrocardiography, *FU* follow up,* Rando* randomisation,* SF-36* Short Form Health Survey (questionnaire)

^*^EOS = end of the entire study is defined as 12 months after randomisation of the last patient

^**^Laboratory tests in screening must be carried out as close as possible to randomisation

(1) Clinical scores include: HE (West Haven Criteria), MELD, MELD Na, MELD 3.0, FIPS, CLIF-C AD, Child-Pugh and NYHA will be documented in eCRF at screening; thereafter, only HE (West Haven Criteria) and NYHA will be collected in eCRF beginning from Visit 3

(2) Only the first paracentesis which is necessary after the study period of 12 months is documented including the date of paracentesis. Further paracenteses after the first one in FU are not considered

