## Interventions

### Explanation for the choice of comparators {6b}

Currently, TIPS implantation is recommended for patients with liver cirrhosis and refractory or recurrent ascites [1, 7]. However, response to treatment (ascites clearance) is often reduced in these patients with advanced liver disease and long-standing decompensation with ascites [13, 15]. Therefore, we hypothesise that early TIPS implantation in selected patients with ascites as the first decompensating event (grade 2 ascites and MELD ≥ 15 or grade 3 ascites) will lead to a higher rate of ascites clearance and improved transplantation-free survival. Therefore, patients with grade 2 ascites and MELD score ≥ 15 or grade 3 ascites as the first single decompensating event will be randomised in an early TIPS group in addition to standard of care and in a SMT group. Patients in the SMT group will be treated following current evidence-based treatment guidelines [1], and therefore, the SMT group reflects the current approach in treatment of patients with ascites. All patients (also including patients in the TIPS group) are advised to adhere to moderate restriction of sodium intake (80–120 mmol/day = 4.6–6.9 g of salt) according to the current EASL guidelines [1, 16]. Treatment of ascites will be performed according to current evidence-based treatment guidelines. Diuretic treatment (using an anti-mineralocorticoid drug and/or loop diuretics) will be used by clinical judgement under regular control of renal function, sodium and potassium values. The body weight loss should not exceed 0.5 kg/day in patients without peripheral oedema and 1 kg/day in the presence of peripheral oedema. The dose of diuretics can be increased after 72 h of treatment until the maximum dose (spironolactone, 400 mg/day; furosemide, 160 mg/day; torasemid, 40 mg/day) is reached or diuretic-induced complications occur [1, 16]. Diuretic-induced complications are defined as acute kidney injury (defined according the KDIGO criteria) and/or diuretic-induced hyponatraemia (decrease of serum sodium by > 10 mmol/l or to a serum sodium < 125 mmol/l) and/or diuretic-induced hypo-or hyperkalaemia (changes in serum potassium to < 3 mmol/l or > 6 mmol/l despite appropriate measures) and/or disabling muscle cramps.

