SF-36 and CLDQ will be compared between treatment arms at two different timepoints (months 6, 12). At both timepoints, a mixed linear model for repeated measures (MMRM) is used modelling the respective scale at this and the earlier timepoints, and including randomised treatment and the baseline value of the respective subscale and centre as covariates. Two-sided *p* values of the tests of the hypotheses that the treatment effect is zero at the respective timepoints will be calculated from these models. As estimates of the effect sizes, the differences of adjusted means (TIPS arm vs.SMT arm) will be calculated with two-sided 95% CI.

The total number of AEs, the minimum, maximum and mean number of adverse events (AEs) per patient, the total number of follow-up (FU) days (number of days in the observation period), the number of AEs per FU-day (total number of AEs divided by the total by the number of follow-up days), the number of patients who had at least one AE and the number of patients who stopped treatment due to AE will be given.

The probability of AEs defined by preferred term (PT) according to MedDRA and of AEs defined by system organ class (SOC) according to MedDRA will be estimated by the Aalen-Johansen estimator. For this purpose, the time from randomisation to the first occurrence of the specific type of AE (defined by PT or defined by SOC) will be analysed. For patients not experiencing the specific type of AE, the time to the end of the documentation period or death, whatever occurs first, will enter the analysis and will be treated as a competing event. This will result in probability estimates (cumulative incidences) for the different AE types (defined by PT and by SOC) over time. The results will be displayed in summary tables by showing the cumulative incidences at the maximum observation time. Incidences of AEs will be calculated with 95% confidence intervals. Additionally, the number of non-serious AEs will be summarised by PT and by SOC.

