### Adverse event reporting and harms {22}

An adverse event (AE) in this study is defined as any untoward medical occurrence/complication in a patient who underwent TIPS or received SMT and which does not necessarily have to have a causal relationship with the TIPS implantation or received therapy.

Table 5 summarises the parameter/adverse events that will be documented to monitor interventional and SMT safety.

**Table 5 Tab5:** Parameter/adverse events that will be documented to monitor interventional and SMT safety

**During TIPS procedure**	**After the end of the procedure AEs related to TIPS implantation**	**For all patients **
• Injury to carotid artery (perforation) • Procedural pneumothorax • Injury to hepatic artery (perforation/puncture) • Liver capsule perforation • Bile duct injury • Arrhythmia • Allergic reaction • Injury to surrounding organs • Intra-abdominal bleeding • Other	• Complications related to the shunt: – TIPS thrombosis – TIPS dysfunction • Contrast media toxicity • Fistula formation • Other directly related to TIPS procedure	• Bleeding oesophageal varices • Hepatic encephalopathy (HE) beginning from grade II [25] • Spontaneous bacterial peritonitis (SBP) • HRS-AKI • Acute kidney injury (AKI) • Acute on chronic liver failure (ACLF) • Diuretic-induced complications • Cardiac failure (according to NYHA class) • Ischemic hepatitis • Infections • Hepatocellular carcinoma (HCC) (including at least BCLC staging, tumor diameter, vascular invasion etc.) • Other

Adverse events have to be documented in the eCRF starting from the date of ICF signature and until end of the study with the following information: characterisation of the event (listed complication, see above [diagnosis or symptoms, if diagnosis not yet available]), onset/end date, severity according to the current version of CTCAEv5, relationship to procedure (yes/no) or to the shunt (yes/no), serious/non-serious and outcome.

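### Before month 1, Table 3 schedules adverse-event, laboratory and encephalopathy checks only in the TIPS arm, so early non-serious events have an extra scheduled chance of detection after TIPS

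*Protocol article*

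**What the plan says.** All places are in the protocol article.

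- **Participant timeline {13}, Table 3.** Visit 2 (day 1 to 7) is headed "after Rando (only TIPS group"), and Visit 3 (discharge, 4 days after the intervention, window +7/-2 days) is likewise marked "only TIPS group". Adverse events and concomitant medication are ticked at both. Visit 3 also ticks Doppler ultrasound, the row "Laboratory (haematology, clinical chemistry, coagulation"), clinical scores and survival status. The next visit, shared by both arms, is Visit 4 at 1 month "after Rando (+ 2 weeks").
- **Table 3, footnote 1.** After screening, "only HE (West Haven Criteria) and NYHA will be collected in eCRF beginning from Visit 3". SMT patients have no Visit 3.
- **Adverse event reporting and harms {22}, Table 5.** The list for all patients includes AKI, HRS-AKI, diuretic-induced complications and "Hepatic encephalopathy (HE) beginning from grade II". Documentation runs from consent to the end of the study in both arms.
- **Explanation for the choice of comparators {6b}.** Diuretic-induced complications are defined by KDIGO criteria and by numerical sodium and potassium limits, or by disabling cramps. Renal function and electrolytes are to be checked regularly on diuretics, with no frequency given. "The dose of diuretics can be increased after 72 h of treatment", so titration can fall within the first weeks.
- **Statistical methods {20a}.** Adverse-event incidence uses "the time from randomisation to the first occurrence of the specific type of AE", shown as cumulative incidence at the maximum observation time. The safety set is grouped by treatment received.

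**The concern.** Events of the same kind are recorded in both arms on one clock, but in the first month the scheduled opportunities to find them differ by arm. This matters most for events that exist in the data only if blood was drawn or the patient was examined at the right moment: a brief creatinine rise, a sodium or potassium excursion, a short encephalopathy episode.

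Because the analysis uses the first occurrence, an episode found at Visit 3 stays in the TIPS estimate for the rest of follow-up. An identical SMT episode that nobody tested for never enters. The trial is open and nothing in the analysis offsets the difference. What is at stake is the fairness of the early, non-serious part of the safety comparison, which would tilt against TIPS and under-record early SMT events.

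**Working it through.** The plan gives no figure on this point, so there is none to reproduce. The check is a count of Table 3 entries, some calendar arithmetic and one illustration.

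**1. When the first scheduled checks fall**

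- Visit 3, earliest: day 1 + 4 - 2 = day 3.
- Visit 3, latest: day 7 + 4 + 7 = day 18.
- Visit 4: about day 30 to 30 + 14 = day 44.
- SMT patients: 134 / 2 = 67 under 1:1 allocation.

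**2. Scheduled checks after day 0 and before Visit 4**

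| Check | TIPS | SMT |
|---|---|---|
| Adverse-event query | 2 (Visits 2 and 3) | 0 |
| Laboratory set | at least 1 (Visit 3) | 0 |
| West Haven and NYHA | 1 (Visit 3) | 0 |

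The Visit 2 laboratory cell is not readable in the text available, so it is not counted.

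**3. Illustration of the mechanism (assumptions mine, not the plan's)**

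Let a laboratory abnormality last D days, with onset uniform over days 0 to 30. It is seen only if a scheduled laboratory test falls within it. Visits are uniform in their windows: TIPS on day 1 to 7, Visit 3 at 2 to 11 days later, Visit 4 on day 30 to 44.

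- *SMT (Visit 4 only).* P = (1/14) × ∫₀ᴰ (D - x)/30 dx = D²/840 for D ≤ 14. D = 3: 9/840 = 0.011. D = 7: 49/840 = 0.058. D = 14: 196/840 = 0.233.
- *TIPS (Visit 3 or Visit 4).* Visit 3 adds E[min(D, day of Visit 3)]/30. For D = 3 this is 3/30 = 0.100, because Visit 3 is never before day 3, and the total is 0.100 + 0.011 = 0.111. Simulation with 400,000 draws gives 0.111, 0.286 and 0.578 for D = 3, 7 and 14.

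| Duration | Seen, TIPS | Seen, SMT |
|---|---|---|
| 3 days | 11% | 1% |
| 7 days | 29% | 6% |
| 14 days | 58% | 23% |

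These figures show direction only. They leave out routine-care tests, which occur in both arms and would narrow the gap. The plan gives no frequency for those tests, so the narrowing cannot be computed.

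**4. How the difference reaches the results**

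The effect on cumulative incidence persists only in patients with no later recorded event of the same type. Anyone with a later AKI, for example, is counted as having had AKI in either arm by the end of follow-up. The total and per-patient event counts in {20a} take in every extra detection.

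**The case against.** The strongest reply is that monitoring is not confined to visits. Adverse events must be entered from consent onward in both arms, and renal and electrolyte values are checked routinely on diuretics. Laboratory data are kept in source documents (Frequency and plans for auditing {23}), and encephalopathy medication is recorded (Relevant concomitant care {11d}). Visits 2 and 3 are the procedure and the discharge after it, so SMT has no natural counterpart. The adverse-event paragraphs of {20a} plan no between-arm test and no month-1 contrast, and five visits from month 1 to month 12 are shared.

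Most of this stands and sets the limits of the point. It does not remove it: the routine provisions apply in both arms, have no stated frequency and add no SMT entry to Table 3. The TIPS-only visits therefore remain an additional opportunity.

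Several stronger readings are tempting but not supported:

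- *SMT patients go unchecked for a month.* Only scheduled trial checks are absent.
- *Early SMT laboratory events are lost for good.* Values drawn in routine care can be retrieved. Only episodes that were never tested are lost.
- *Mild encephalopathy is over-counted after TIPS.* Table 5 starts at grade II, so grade I is not a listed event.
- *The data monitoring committee is misled.* It is informed of adverse events, but under {21a} it evaluates mortality and serious events, which depend least on one extra blood draw.
- *Efficacy is biased.* Death and transplantation can be dated at later visits.

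**Conclusion.** The point holds for scheduled ascertainment. Before Visit 4 the TIPS arm has two adverse-event queries and at least one laboratory and encephalopathy set that SMT lacks, and these feed an analysis whose clock starts at randomisation. The expected direction is higher early non-serious counts for TIPS relative to SMT, mainly for silent or transient laboratory-defined events and short grade II or higher encephalopathy episodes.

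The size cannot be computed from the documents, since it depends on how often routine tests are done and how long such episodes last. The weight is minor to moderate: a weakness of the descriptive safety comparison that is cheap to reduce, with no material effect on the primary endpoint. Collection needs to change because an analysis plan cannot supply values or gradings that were never obtained.

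**What to change.** 1. **Collection.** Add to Table 3 one SMT contact, by ward visit or telephone, in the Visit 3 calendar window (about day 3 to 18). It would carry an adverse-event query, an encephalopathy query and transcription of renal and electrolyte values already drawn in routine care. No new procedure or blood draw is needed.
2. **Reporting.** Keep the analysis from randomisation. Alongside it, show AKI, electrolyte and encephalopathy incidence from Visit 4 onward. Show the Visit 2 and 3 findings also as peri-procedural TIPS data, so that procedural harm stays visible. The Visit 4 table conditions on reaching that visit, so it is descriptive and must not replace the main analysis.

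**Cost.** About 67 short contacts, one eCRF form and one extra table, introduced by amendment. Patients already past the window cannot have the contact, though their routine values could still be transcribed. A single contact does not match in-hospital observation after a procedure, so the asymmetry is reduced rather than removed. The report should say so.

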### Sample size {14}

Sample size calculation is based on the primary endpoint transplantation-free survival (TFS), defined as time from randomisation to liver transplantation or death. It is assumed that the TFS probability of patients in the control group (SMT) is approximately 66% after one year. With an assumed TFS rate of approximately 82% in the TIPS group, this corresponds to a hazard ratio of 0.48 of the TIPS group compared to the control group (SMT group). The assumption is based on the study by Bureau et al. that analysed 62 patients. The one-year rate of TFS in the TIPS group was 93% (95%CI, 82%–100%) [12]. The TFS probability of the SMT group was assumed according to data from patients with first decompensation with ascites in the INCA trial (unpublished data [24] and, the data provided by Balcar et al. that report1-year TFS in patients with LVP [14]. The effect of TIPS implantation will be assessed by a test at two-sided significance level of 5% and by estimation of the hazard ratio with corresponding asymptotic two-sided 95% confidence interval. The null hypothesis is rejected if the confidence interval does not contain one. Under the above assumptions, the study is planned to detect a difference between the experimental intervention (TIPS group) and the control group (SMT group) with a power of 80%, which requires a total number of 57 events to be observed. The required number of patients to be randomised to observe this amount of events depends on the length of follow-up. With a recruitment period of three years, an additional follow-up period after the end of recruitment of two years, it can be safely assumed that a sufficient number of events will have been observed by the end of the trial if 116 patients are available for analysis (software used, e.g. n Query Advisor 8.3). Furthermore, the exponential drop-out rate is assumed to be 0.01. Therefore, 134 patients will be randomised. Before the end of the planned recruitment phase, a blinded assessment of the TFS rate (both treatments combined) will be performed. If the TFS rate appears to be higher than anticipated, the recruitment phase will be extended, and the required number of patients will be calculated anew under the amended assumptions. Irrespective of this sample size amendment, the analysis will be conducted after the observation of 57 events as planned, so no alpha adjustment is necessary.

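### The blinded review is triggered by the pooled TFS rate rather than by projected events, so it does not respond to drop-out that could leave the trial short of its 57 events

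*Protocol article*

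**What the plan says.** All of this is in Sample size {14} of the protocol article unless noted.

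- Planning assumptions: a one-year TFS of about 66% under SMT. For the comparison the section states: "With an assumed TFS rate of approximately 82% in the TIPS group, this corresponds to a hazard ratio of 0.48".
- Target: "with a power of 80%, which requires a total number of 57 events to be observed".
- What reaching the target depends on: "The required number of patients to be randomised to observe this amount of events depends on the length of follow-up". Drop-out also enters: "Furthermore, the exponential drop-out rate is assumed to be 0.01", with no time unit. The section takes 116 patients as analysable and 134 as randomised, with three years of recruitment and two further years of follow-up.
- Review: before recruitment ends, the TFS rate of both arms combined is assessed blind. "If the TFS rate appears to be higher than anticipated, the recruitment phase will be extended", and the same sentence goes on to say that the number of patients is then recalculated under amended assumptions.
- Analysis: whatever the review leads to, "the analysis will be conducted after the observation of 57 events as planned", which is the reason given for not adjusting alpha.

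The footnote to Table 3 (Participant timeline {13}) ends the whole study 12 months after the last randomisation. That does not agree with the two years above.

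**The concern.** The quantity that has to be protected is the number of events. It depends on the event hazard, the drop-out hazard, accrual and the length of follow-up. The rule looks at the first of these only, and it is the only stated way of enlarging the trial.

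Two consequences follow. First, extra drop-out reduces events and leaves the trigger unmoved, so a trial heading for fewer than 57 events can pass its review. Second, the wording attaches no margin and puts the extension before the recalculation. Read literally, it extends on any excess over the anticipated rate, needed or not. At stake are the stated 80% power on one side and avoidable recruitment on the other.

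**Working it through.** **Inputs from the protocol.** One-year TFS 0.66 and 0.82, 1:1 allocation, 57 events, 134 randomised, 3 years' recruitment (R = 3), follow-up F of 1 year (Table 3 footnote) or 2 years (Sample size {14}), drop-out 0.01.

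**Assumptions.** Exponential times, uniform accrual, non-informative drop-out, a Kaplan-Meier estimate at the review, a review at month 30, and any excess over the planned rate counting as higher. The unit of 0.01 is tried both per year and per month (0.12 per year). The hazard of 0.24 per year is a scenario, twice the monthly reading; it means a loss of 1 − exp(−0.24) = 21% per year.

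**1. The plan's own event number.** The hazards are −ln 0.66 = 0.4155 and −ln 0.82 = 0.1985 per year, ratio 0.4776. Schoenfeld: 4(1.960 + 0.842)² / (ln 0.4776)² = 57.5. With 57 events the power is 79.7% (79.1% at a ratio of 0.48). The figure of 57 is reproduced within rounding.

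**2. Expected events.** For hazard λ and drop-out hazard δ, with t = λ + δ, the probability of an observed event is

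p = (λ/t) × [1 − (exp(−tF) − exp(−t(R+F))) / (tR)],

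and expected events are 67 × (p for SMT + p for TIPS).

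| Drop-out hazard per year | F = 1 | F = 2 |
|---|---|---|
| 0.01 | 66.6 | 82.2 |
| 0.12 | 59.0 | 70.7 |
| 0.24 | 52.3 | 60.8 |

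Example, F = 1 and δ = 0.24: 67 × (0.490 + 0.290) = 52.3. Expected events drop below 57 at a drop-out of about 14% per year with F = 1 and about 26% with F = 2. The monthly reading of 0.01 is 1 − exp(−0.12) = 11.3% per year. With F = 1, 116 patients without drop-out give 58.3 events and 134 with 0.01 per month give 59.0. The stated patient numbers therefore fit that combination and leave about two events to spare.

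**3. How often the trigger fires.** The anticipated pooled one-year TFS is (0.66 + 0.82)/2 = 0.74. In simulation the estimate at month 30 has a standard error of about 4.7 to 5.0 points and exceeds 0.74 in 50–53% of trials. This holds at every drop-out level tried.

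**4. What the recalculation then asks for.** Keep the hazard ratio, scale both hazards by a common factor, and find the pooled TFS at which 134 patients yield exactly 57 events. Above it, more than 134 are needed.

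| Drop-out used in the recalculation | F = 1: threshold, share of trials | F = 2: threshold, share of trials |
|---|---|---|
| 0.01 per year | 78.7%, about 17% | 84.4%, about 1% |
| 0.01 per month | 75.1%, about 42% | 80.7%, about 8% |

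The shares are simulated. A normal approximation agrees: (78.7 − 74)/4.7 = 1.0 standard errors gives 16%, and (75.1 − 74)/4.8 = 0.23 gives 41%.

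**5. Shortfalls the trigger misses.** At 0.24 per year with F = 1, 77–80% of simulated trials fall short of 57 events and 32–35% fall short with no trigger. At 0.12 per year, about 33% fall short and 10% do so untriggered. At 0.24 per year with F = 2, about 7% fall short untriggered.

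**6. An event projection instead.** A rule that fires when the blinded projection is below 57 fires at 0.01 per year in about 10% of trials (F = 1) or 0.1% (F = 2). At 0.01 per month it fires in 37% or 4%, and at 0.24 per year with F = 1 in 72–73%. Unlike the TFS trigger, it rises with drop-out.

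**The case against.** A reader might infer from step 3 that the review is a coin flip that needlessly lengthens half of all on-course trials. The document does not support this. The trigger sentence goes on to a recalculation, and that is the second filter in step 4. Where there is ample slack (0.01 per year), few trials would be asked for more than 134 patients. Where more are asked for (0.01 per month, 12 months), the trial has almost no spare events, so many of those extensions are warranted. The literal reading, extending even when the new number is 134 or fewer, survives only as a point about wording and order.

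A reader might also infer that the drop-out gap is serious whichever end of study applies. It is not: with two years of follow-up, expected events stay above 57 even at 0.24 per year.

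Nor is the review the sole protection. Holding the analysis until 57 events would turn a shortfall into a delay. However, the fixed end in Table 3 conflicts with waiting, and the two places need reconciling.

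Finally, the margin, estimator and review date may be set in the full protocol or SAP. A margin would cut false alarms but would not make TFS respond to drop-out. A crude proportion that counts drop-outs as event-free would rise with drop-out, so the insensitivity depends on a Kaplan-Meier type estimate. Blinded review of a pooled rate is an accepted design. What stands is that the chosen quantity is not the one the analysis depends on.

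**Conclusion.** The point holds as a cheap improvement to a stated rule. The firmer weakness is that the trigger does not react to drop-out above the assumed rate. Under the 12-month end of study and an assumed drop-out of 0.24 per year, about a third of trials would miss 57 events with no extension triggered; under two years of follow-up, about 7%. The weaker part is that a literal trigger with no margin is met in about half of on-course trials, while the recalculation would enlarge the trial in 1% to 42% of them, depending on the unit of the drop-out rate and the end of follow-up. Alpha is not affected in either case. The sizes rest on the assumptions listed with the working, above all the drop-out scenario and the Kaplan-Meier estimate.

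**What to change.** Replace the trigger in Sample size {14}. At a fixed date before recruitment ends (month 30, for example), use pooled data to project the number of TFS events by the planned end of follow-up from the pooled event hazard, the pooled drop-out hazard and actual accrual. Extend recruitment, follow-up or both only if the projection is below 57. Keep the analysis at 57 events, so that the argument for no alpha adjustment stands. The projection needs a single end date, so the 12-month and two-year statements must be reconciled, and the time unit of the drop-out rate should be given.

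The cost is about two sentences and a short blinded calculation on data already collected. The downside is that drop-out as well as high TFS may then lead to an extension.
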